## Abstract

**Background:**

Psychoeducation is included in the Norwegian national guidelines for treatment of adult ADHD. Despite some promising results for the treatment of other conditions and ADHD, little is known about the efficacy of such interventions. This paper presents a protocol for a pilot randomized controlled trial featuring a psychoeducational group program for patients with ADHD. The main objective of this pilot trial is to investigate adherence, feasibility, and preliminary efficacy of a ten-session psychoeducational group designed to address specific challenges faced by adults diagnosed with ADHD.

**Methods:**

This pilot study will evaluate patient satisfaction and preliminary efficacy of a psychoeducational group treatment using a randomized waitlist-controlled trial at two different outpatient clinics in mid-Norway. All participants will receive treatment as usual, concomitant with the intervention and waitlist period. Client satisfaction (CSQ 8), general self-efficacy (GSE-6), ADHD-related quality of life (AAQoL), symptoms of ADHD (SCL-9; ASRS), and work participation will be assessed at the time of recruitment prior to randomization (T0), pre-intervention (T1), post-intervention (T2), and at 10 weeks follow-up (T3). Recruitment and dropout rates along with treatment adherence will also be evaluated.

**Discussion:**

This study offers valuable insight into the preliminary efficacy of educational programs implemented in outpatient clinics. The aim of the trial is to evaluate adherence, feasibility, patient satisfaction, and the preliminary efficacy of a psychoeducational group intervention for patients with adult ADHD and provide further insight into the design and construction of a large-scale trial. The results also offer preliminary empirical evidence to inform the development of larger and more complex studies.

**Trial registration:**

NCT03337425, Registered 9 November 2017

## Background

ADHD is a common disorder [1] that continues from childhood into adulthood in 30 to 60% of cases [2, 3]. In a large multinational study, the average prevalence rate has been estimated to be 3.4% among adults [4]. ADHD is characterized by difficulties with regard to attention, hyperactivity, and impulsivity. In addition to these persistent problems, patients often struggle with psychiatric comorbidity [5–9]. The results from previous studies indicate that as many as 90% of adult patients with ADHD struggle with one or more comorbid psychiatric conditions [10]. Of these, the most common comorbid conditions are anxiety disorders, affective disorders, substance abuse, antisocial personality disorders, and developmental disorders, such as autism and learning difficulties. ADHD among adults is also associated with impaired function in areas that include psychosocial functioning, education, work [11, 12], and executive function [1, 13]. There are minimal differences between genders in terms of symptoms, comorbidities, and function in adults with ADHD [8, 14, 15].

Previous studies [16, 17] and the “Consensus of the European Network of Adult ADHD” [18] have pointed out the importance of psychoeducation as an intervention in the treatment of adults with ADHD. These recommendations suggest that psychoeducation could offer understanding of previous difficulties and improve general functioning. Psychoeducation is not directly process-oriented, but it is effective as a therapeutic intervention for bipolar disorder [19, 20]. The results indicate higher levels of treatment compliance, better psychosocial functioning, and improved overall outcomes. Similar results have also been reported among patients with psychosis: a documented reduction of readmissions to hospital, increased compliance, and improved quality of life [21, 22].

We searched PubMed and PsycINFO and found only one randomized controlled pilot study of psychoeducation for ADHD among adults. In this study [23], a series of 11 psychoeducational sessions related to clear ADHD-specific challenges were compared with cognitive behavioral group therapy. The results indicated that both types of treatments reduced symptom severity and the negative effects of symptoms, diminished hyperactivity and impulsiveness, and improved attention and self-esteem. Patients also reported a decrease in anxiety and depression symptoms; 93.8% of patients completed the intervention. We also found a non-controlled, pilot study of psychoeducational groups for adults with ADHD and their significant others based on elements of CBT, neuropsychology, and results from interdisciplinary ADHD research. The intervention was conducted at three different clinics in Sweden and comprised 41 patients and 40 significant others. The results suggested there is an increase in knowledge of ADHD, quality of social relations, and psychological well-being after treatment [24].

Even though the results of these studies are promising, more controlled trials are needed to assess the efficacy of psychoeducation for adults with ADHD. Thus, there is a necessity to evaluate patient satisfaction and the short-term effects of psychoeducational group interventions in clinical settings. This study protocol describes an innovative education group intervention where health personnel and representatives from the ADHD user organization educate adults with ADHD to improve self-management. User involvement will occur during the intervention delivery phase. Representatives from user organizations will be peer educators co-leading two sessions. The intervention will be delivered at two centers, of which the center that has developed the intervention has limited experience with the research procedures needed to conduct a proper trial. The other center has no previous experience delivering the intervention. In order to plan a definitive trial, we must investigate the feasibility of both the research and intervention procedures, as well as evaluate patient satisfaction within the context of the intervention. We require information on how many patients will complete the intervention with evaluable data, as well as insight into the feasibility of randomization procedures and estimates of parameters required for sample calculation. This intervention is based on active participation and exchange of experiences between the participants. Measuring patient satisfaction is also an important part of fine-tuning the intervention before a large-scale trial. Hence, the purpose of our study was to investigate the feasibility, preliminary effects, and patient satisfaction with a group-based psychoeducational program consisting of ten sessions delivered to adults with ADHD using a prospective, randomized, and controlled study design.

## Methods

### Study design

This protocol describes a multicenter trial to study patient satisfaction and the preliminary efficacy of a group-based psychoeducational program for adults with ADHD and is available online at ClinicalTrials.gov (NCT03337425). The study will be reported in accordance with the Template for Interventions Description and Replication and the Consolidated Standards of Reporting Trials.

Patients from two different outpatient clinics (Nord-Trøndelag Hospital Trust and Tiller District Psychiatric Centre) will be included. The treatment is available for patients in the Nord-Trøndelag Hospital Trust for 4 years, but it has not been evaluated nor has it been implemented at the other center. Therefore, a pilot study is warranted. All patients included in the study will receive treatment as usual concomitant to psychoeducation or waitlist. Patients will be recruited and randomly assigned to condition A, psychoeducation + treatment as usual, or condition B, waiting list + treatment as usual. There is a need for at least 30 subjects in each cohort. Eligible outpatients diagnosed with ADHD at one of the outpatient clinics could be enrolled. The inclusion and exclusion criteria are listed in Table 1, and the recruitment procedure and assignment to conditions are found in Fig. 1.

**Table 1 Tab1:** Inclusion and exclusion criteria

Inclusion criteria	Exclusion criteria
Age between 18 and 67	Unable to give informed consent
Speaking a Scandinavian language	Psychosis
Confirmed ADHD diagnosis	Severe learning difficulties

**Fig. 1 Fig1:**
[figure not shown]
Recruitment procedure and assignment to conditions

#### Condition A: Psychoeducation concomitant with treatment as usual

Both conditions A and B received treatment as usual (see description under the “Condition B: Waiting list concomitant with treatment as usual” section) in addition to psychoeducation or waitlist. The group-based psychoeducational program consists of ten sessions that were ran over ten consecutive weeks. Each session consists of a lecture from a recruited expert on the topic of the session (20 min) with a following discussion of the topic (45 min) facilitated by the course leader (Table 2). All sessions are organized and led by the course leader, which also includes structured time, discussion, and closing of the session.

**Table 2 Tab2:** Topic for sessions

Topic and main focus for session	Lecturer (in addition to course leader)
Introduction and presentation of the intervention Myths and facts about ADHD	Given by the course leader (nurse) and expert in ADHD (social worker or psychologist)
What is ADHD?	Nurse or social worker or psychologist with ADHD expertise
Inattention	Nurse or social worker or psychologist with ADHD expertise
Impulsivity	Nurse or social worker or psychologist with ADHD expertise
Hyperactivity	Nurse or social worker or psychologist with ADHD expertise.
ADHD and comorbidity	Medical doctor, psychologist, or experienced psychiatric nurse
Use of medications	Medical doctor specialized in ADHD
Economy	Social worker
Work and welfare	Representative from the public welfare agency Representative from ADHD Norway
Summary and closing session	Led by the course leader

#### Condition B: Waiting list concomitant with treatment as usual

Treatment as usual consists of treatment with ADHD medication for most patients. Additionally, certain patients would normally receive counseling or psychotherapy, although this is not systematically provided to every patient; thus, the randomization procedures are necessary to reduce this as a possible bias. If needed, patients are also offered assistance with regard to economy, housing, education, and work as well as contact with family and their network. The participants allocated to the waiting list control group were told to live as normal and continue with treatment.

### Data and measurement

Clinical symptoms and function will be measured at the time of recruitment prior to randomization (T0), pre-intervention (T1), post-intervention (T2) as well as at 10 weeks follow-up (T3). The waitlist-control group will have two additional measurements during the pre- and post-waiting period. Measuring patient satisfaction and change in symptom load, general self-efficacy, quality of life, and function can serve as indicators of the preliminary efficacy of the intervention. The assessments and measurements are listed in Fig. 2.

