### Statistics

Statistical analysis will be conducted using SPSS [34] and STATA [35]. In order to calculate preliminary effects, chi-square statistics and *t* tests will be used for descriptive analyses of categorical and continuous variables, respectively, in addition to analysis of variance (ANOVA) for comparison of results for the control and experimental groups. Possible other predictors for the preliminary efficacy of psychoeducation will be examined using linear regression on the total sample (pre-post intervention). Intervention adherence will be calculated by assessing the response rate of participants receiving the intervention, response rate of returned questionnaires, and the number of sessions completed by intervention group participants. Recruitment and dropout rates will be evaluated using absolute and percentage frequencies.

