### Main study and decision to proceed

The pilot study utilizes the same design as the intended main study to make a proper decision on whether to proceed or not. The decision to proceed will be based on the measurement of client satisfaction as well as the preliminary efficacy of ADHD-related symptoms and quality of life. With this, our study may influence the clinical practice and short-term results to empower patients in the management of their own symptoms and health treatment. The short-time impact of the intervention on function is unclear. If the decision is to proceed, then the long-term effects of the intervention will be assessed in a new main study employing the same design but with an additional 3 or 6 months of follow-up.

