### Methodological weaknesses

This study is not double-blinded nor did we use the “placebo intervention” other than the waiting list owing to ethical considerations. We do not compare our model to another form of treatment other than treatment as usual, but this is because there is a lack of a gold standard for psychoeducational interventions in adult ADHD. The waiting list group design has certain weaknesses, but considering the ethical aspects requiring that all patients receive treatment, the interventions were important (waiting lists are typical in these clinics).

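### The waitlist design gives one randomised programme-versus-no-programme comparison after baseline, so a main study of the same design cannot assess controlled long-term effects

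*Protocol article*

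**What the plan says.** Under Study design, patients are "randomly assigned to condition A, psychoeducation + treatment as usual, or condition B, waiting list + treatment as usual". Under Data and measurement there are four labelled occasions: T0 before randomisation, T1 before the intervention, T2 after it, and T3 ten weeks later. The same paragraph adds: "The waitlist-control group will have two additional measurements during the pre- and post-waiting period".

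Under Statistics, the between-arm analysis is "analysis of variance (ANOVA) for comparison of results for the control and experimental groups". No occasion is named. A separate linear regression for predictors uses pre-to-post intervention data from the whole sample.

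Methodological weaknesses justifies the waiting list by "the ethical aspects requiring that all patients receive treatment". Main study and decision to proceed bases that decision on client satisfaction and preliminary efficacy. It adds that, if the trial goes on, "the long-term effects of the intervention will be assessed in a new main study employing the same design", with a further 3 or 6 months of follow-up.

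**The concern.** A waitlist arm is a control only while it waits. T1, T2 and T3 are defined by the intervention, so in arm B the T2 and T3 labels fall after its own delayed programme. Two consequences follow.

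- The Discussion's sentence on long-term effects promises something the design cannot give under randomisation. Once arm B has had the programme, later change in either arm cannot be separated from regression to the mean, natural course or changes in treatment as usual, which the article says is not uniform across patients.
- The ANOVA is not tied to the one occasion on which arm B is an untreated comparator. The Background wants parameter estimates for the main study's sample size, and the decision to proceed rests partly on preliminary efficacy. An estimate from the wrong pair of occasions would feed into both.

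**Working it through.** **Step 1. Does arm B receive the programme?** No sentence shown gives its start, so this is an inference from three places.

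- Data and measurement: arm B's waiting-period measurements are additional to T0–T3, which makes sense only if arm B also has its own T1–T3 around a programme.
- Statistics: pre-post intervention data are expected from the total sample.
- Methodological weaknesses: all patients are to receive treatment.

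All three point the same way.

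**Step 2. Count the controlled occasions.** Arm B has one pre-waiting and one post-waiting measurement. Only the second can show a difference between programme and no programme, so there is one controlled post-baseline comparison. T1 also follows T0 but precedes the programme in both arms, so it carries no programme effect.

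**Step 3. Calendar.** Inputs from the article: programme 10 weeks, T3 10 weeks after T2, main-study extension 3 or 6 months (taken as 13 or 26 weeks). The wait, w, is not stated in the text shown and is assumed. With week 0 as arm A's programme start:

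- Arm A: T2 = 10; T3 = 10 + 10 = 20; extended follow-up = 20 + 13 = 33 or 20 + 26 = 46.
- Arm B: post-waiting = w; programme ends = w + 10; T3 = w + 20.

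| Assumed wait w (weeks) | B post-waiting | B programme ends | B at T3 | B untreated at A's T2 (week 10) | B untreated at A's T3 (week 20) | B untreated at week 33 or 46 |
|---|---|---|---|---|---|---|
| 10 | 10 | 20 | 30 | yes | no | no |
| 15 | 15 | 25 | 35 | yes | no | no |
| 20 | 20 | 30 | 40 | yes | yes | no |

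With a wait of 20 weeks, arm B would still be untreated at arm A's T3, but there is one post-waiting measurement, so there is still one controlled occasion. For arm B to be untreated at the extended follow-up, the wait would have to reach 33 or 46 weeks.

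**Step 4. What is at stake in the choice of comparison.** The article gives no effect size, SD, alpha or power. Its 60 patients are 2 × 30, set on practical grounds, so there is no power figure to reproduce. As an illustration only, take 30 per arm, two-sided 0.05, a normal approximation and assumed standardised effects d. The standard error is √(2/30) = 0.258. The rejection probability is Φ(δ/0.258 − 1.96) + Φ(−δ/0.258 − 1.96), where δ is the expected between-arm difference.

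| Assumed d | A at T2 vs B post-waiting (δ = d) | Same label, B gained half (δ = d/2) | Same label, B gained all (δ = 0) |
|---|---|---|---|
| 0.3 | 21% | 9% | 5% |
| 0.5 | 49% | 16% | 5% |
| 0.8 | 87% | 34% | 5% |

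The last two columns apply only if arms were compared at the same label, which the article does not say.

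**The case against.** A reader might infer that the planned ANOVA compares treated with treated patients and so drives the estimate to zero. The documents do not support that. Statistics names no T2-with-T2 or T3-with-T3 comparison. The waiting-period measurements exist, evidently, to supply untreated control data, and the ANOVA is described separately from the pooled pre-post regression. Read together, these point towards the valid comparison. The zero difference also needs an effect that is equal in both arms and persists, which is an assumption. Naming the exact pair of visits may be left to an analysis plan that is not shown, and the figures on allocation and schedule, also not shown, may give the calendar. All of this stands, and it makes the Statistics part of the point conditional.

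It can also be said that the article claims only short-term and preliminary effects for the pilot, concedes weaknesses in the waiting list, and mentions the main study only as a possibility. That is fair for the pilot's T3: no controlled T3 effect is claimed. It does not rescue the main-study sentence, which says what the same design will assess. No analysis plan for the pilot can supply the missing comparator, and the conceded weaknesses do not name this one.

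Adjusting for T0 rather than the pre-waiting value is partly a preference. The case for T0 is that both arms have it and it precedes randomisation.

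**Conclusion.** The point holds, at moderate severity. Arm A at T2 against arm B post-waiting is the only randomised programme-versus-no-programme comparison after baseline. The sentence on long-term effects is wrong as written: at about week 33 or 46 the same design would have no untreated randomised control and could describe only uncontrolled maintenance within arms.

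This rests on the inference that arm B receives the programme after waiting, and on an assumed wait of about 10 to 20 weeks. If the schedule figure shows a wait near 20 weeks, the post-waiting measurement would line up in time with arm A's T3 rather than T2; the count of one controlled occasion would not change.

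No error in the planned ANOVA is shown. There is a risk if the comparison is made by label. In a 60-patient pilot sized on practical grounds, with the valid data already scheduled, this calls for correction but does not undermine the trial.

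**What to change.** In Statistics, state that the between-arm efficacy estimate is arm A at T2 against arm B at the post-waiting assessment, by ANCOVA adjusted for T0. State that T3 in both arms, and arm B's own pre-to-post programme change, are reported as within-arm change and not as effects.

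In Main study and decision to proceed, replace the claim about long-term effects. Say that follow-up after the waitlist arm has been treated is uncontrolled, and that a controlled long-term effect would need a comparator maintained through that follow-up.

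The cost is wording and analysis specification: no new data, and no change to when any patient is treated. The downside is that T3 and longer-term results can be reported only as uncontrolled change.

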**Fig. 2 Fig2:**
[figure not shown]
Content for the schedule of enrolment, interventions, and assessments

### Fidelity scale

Fidelity will be assessed with a fidelity scale. The scale evaluates different components of intervention fidelity, such as process fidelity, content fidelity, and quality of interaction. The scale will be completed at ten time points during the intervention delivery phase.

### Medical records

Medical records will be used to collect demographic information, history of medication, as along with information about psychiatric comorbidity. Allowance to use such data is included in the participants’ informed consent.

### Self-reported demographics and questionnaires

Demographic information about age, sex, education, use of healthcare services, and employment status is collected at baseline and T1 with a self-report questionnaire.

#### Client Satisfaction Questionnaire (CSQ-8)

A modified version of the Client Satisfaction Questionnaire (CSQ-8) [25] is included in order to assess satisfaction in relation to the group-based psychoeducational program. The scale consists of eight items measured on a scale from 1 to 4; three of the items are reverse scored. A sum score between 8 and 32 indicates the level of satisfaction with the services provided. The modification of the questionnaire is an additional open question, where the participants may comment on the content and suggest changes to the psychoeducational program.

#### General Self-Efficacy Scale 6-Item (GSE-6)

The GSE-6 is a short-form version of the GSE scale [26]. It will be employed to measure general self-efficacy [27]. Self-efficacy is regarded as a protective factor in adapting to stress and chronic illness. It refers to the belief that one would be able to control and adapt to challenging demands in the future. The scale consists of six items measured on a 4-point scale from “not at all true” (1) to “exactly true” (4). The possible score range is 6–24 with a high score reflecting a higher level of self-efficacy.

#### Adult ADHD Self-Report Scale Full Edition (ASRS)

The ASRS is the World Health Organizations self-reporting scale for ADHD in adults [28]. The scale is designed to examine the current ADHD symptomatology and consists of 18 items based on the DSM-V diagnostic criteria for ADHD. The scale is divided into two parts, and each has a sum score. Questions 1–9 (part A) reflect symptoms of inattention (I), and questions 10–18 (part B) reflect symptoms of impulsivity and hyperactivity (HI).

#### Hopkin’s Symptom Checklist (SCL-90) 9-item

The SCL-90 is a self-report scale for measuring psychiatric symptoms. An ADHD-specific scale consisting of nine items from the original 90 (SCL-9) has been tested and validated for screening. This shows acceptable sensitivity with regard to measuring ADHD symptoms and is a supplement to ASRS. The SCL-9 covers the specific characteristic traits of ADHD with high scores on SCL-9 indicating ADHD-related symptom burden [29].

